## Abstract

People with rheumatological conditions often experience debilitating foot-related symptoms requiring expert multidisciplinary care. However, in Australia there is a glaring gap in the provision of universally accessible, publicly-funded podiatry services. This study aims to assess the feasibility of a randomised trial evaluating a publicly-funded podiatry service for people with foot-specific symptoms related to rheumatological conditions. A pragmatic, participant-blind, parallel-group, randomised feasibility trial will compare effectiveness of a podiatry service with usual care. Consumer interviews will inform the design of the feasibility trial. Thirty adults with a rheumatological condition and foot specific symptoms will be recruited from an outpatient rheumatology clinic and randomised to receive access to a podiatry service or a control group who will receive usual care. Outcome measures will be obtained at baseline, week 6 and week 12. Feasibility will be evaluated using a framework that includes 10 important domains of uncertainty in pragmatic feasibility trials. Secondary outcomes (such as Goal Attainment Scaling) will also be collected and effect sizes of between group differences calculated to signal efficacy. The study will explore the feasibility of conducting a fully powered randomised trial of the effectiveness of a podiatry service for people with a rheumatological condition and foot-specific symptoms. In addition, the trial will determine the feasibility of Goal Attainment Scaling as a primary outcome measure for this population.

Trial registration.

The trial is registered with the Australian and New Zealand Clinical Trial Registry (ANZCTRN12625001000493 on the 9th of September 2025).

## Introduction

People living with rheumatological conditions frequently endure debilitating foot-related symptoms. Studies indicate that up to 90% of adults with rheumatoid arthritis suffer from foot pain, significantly impacting their daily activities and overall well-being [1]. The presence of foot and ankle symptoms correlates with increased disease activity and disability, leading to a diminished quality of life [2]. Moreover, foot ulceration is a prevalent and serious complication among people with chronic rheumatoid arthritis, affecting up to 4–10% of patients [3, 4]. Foot ulceration is not exclusive to rheumatoid arthritis, and is also observed in systemic lupus erythematosus [5], and systemic sclerosis and small vessel vasculitis [6]. Systemic lupus erythematosus, a connective tissue disease, is particularly notorious for affecting the feet, resulting in an array of vascular, dermatological, and musculoskeletal issues [7]. Despite advancements in treatment and the introduction of novel disease-modifying antirheumatic drugs, these foot-specific symptoms may persist, underscoring the need for targeted research and improved management strategies to enhance the quality of life [8, 9].

Rheumatological conditions are complex, and require patient-centred, multidisciplinary approaches that address the many ways these conditions affect health and wellbeing. Patient-centred multidisciplinary team-based care is recommended in the recent Australian Rheumatoid Arthritis Clinical Care Standard [10] and Juvenile Idiopathic Arthritis Standard of Care [11], and is advocated for by Arthritis Australia [12]. However, the reality is that the provision of such care is contingent upon the availability of a diverse team of healthcare professionals. A glaring gap in this team is the provision of podiatric care, which is somewhat of a ‘black hole’ [13]. Previous research has found a stark absence of podiatrists within public rheumatology departments across Australia [14], and there is a significant disconnect in the integration of podiatry into existing care teams [15]. This is despite podiatry-led management of foot symptoms being effective for people with a range of rheumatological conditions [16]. The need for specialised podiatry care is clear and pressing, yet the current system fails to meet this need, which underscores the challenges faced in adhering to the minimum standards of multidisciplinary care.

Recognising the critical role of patient-centred multidisciplinary team care in managing foot-related symptoms for individuals with rheumatological conditions, the need for universally accessible, publicly-funded podiatry services is clear. At present, access to podiatric care is largely restricted to the private sector, creating a significant barrier to equitable health provision. This study aims to assess the feasibility of implementing a pragmatic randomised trial to evaluate the effectiveness and cost-effectiveness of a publicly-funded podiatry service tailored for people suffering from foot-related symptoms due to rheumatological conditions. Furthermore, the study will explore patient-centred goal-setting as an outcome measure and obtain data to inform sample size calculations for a randomised trial.

## Methods

This will be a pragmatic, participant-blind, parallel-group, randomised feasibility trial comparing access to a podiatry service with usual care. The trial is registered with the Australian and New Zealand Clinical Trial Registry (ANZCTRN12625001000493) and has been developed in accordance with the SPIRIT 2025 statement [17], the CONSORT 2010 statement extension to randomised pilot and feasibility trials [18], and the TIDieR checklist for reporting of interventions [19]. Ethics approval has been obtained from the La Trobe University Human Ethics Committee (Approval number HEC25095 on the 20th of May 2025) and written informed consent will be obtained from all participants during the baseline assessment.

The randomisation module in REDCap (Research Electronic Data Capture, Vanderbilt University, USA) will be used to randomise participants. Participants will be allocated on a 1 to 1 ratio with blocking in groups of 4 and 6, and stratification based on sex at birth to ensure a balance of participant sex between the groups. Allocation will be concealed from all researchers until after eligibility screening. Participants will be randomised to their intervention after completing consent at the baseline assessment.

Given this is a feasibility trial, only participants will be blind to their allocation. Both groups will be blind to group allocation through limited disclosure. All participants will be informed that two different types of treatment are being compared, however only the intervention group will be informed about the additional access to podiatry treatment.

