### Other variables: limited efficacy testing

In addition to evaluating feasibility, limited efficacy testing will be undertaken on measures to be included in a fully powered randomised trial. These measures are outlined briefly in Table 2 and in specific detail in Online Resources 2.

**Table 2 Tab2:** Other variables measured for limited efficacy testing

Variable	Outcome measure	Timepoints
Goal attainment	Goal Attainment Scaling	Baseline and week 12
Global change	Global Perceived Rating of Change (15-point Likert scale)	Week 6 and week 12
	Patient Global Assessment	Baseline, week 6 and week 12
Foot-specific pain	Foot Health Status Questionnaire—foot pain domain	Baseline, week 6 and week 12
	Manchester-Oxford Foot Questionnaire—foot pain subscale	Baseline, week 6 and week 12
Foot-specific function	Foot Health Status Questionnaire—foot function domain	Baseline, week 6 and week 12
	Manchester-Oxford Foot Questionnaire—walking/standing subscale	Baseline, week 6 and week 12
Disability	Health Assessment Questionnaire—disability index	Baseline, week 6 and week 12
Stiffness	11-point numerical rating scale	Baseline, week 6 and week 12
Fatigue	Functional Assessment of Chronic Illness Therapy-Fatigue (FACIT-Fatigue) version 4	Baseline, week 6 and week 12
Change in physical activity	Global Physical Activity Questionnaire	Baseline, week 6 and week 12

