### Procedures

The flow of participants through the trial is displayed in Fig. 1. Potential participants will be initially screened via telephone interview against the inclusion criteria by a research assistant, who will enter data into REDCap. The data collected during this screening telephone interview is outlined in Online Resource 3. During eligibility screening, if the participant is eligible for inclusion an appointment will be made for the baseline assessment with the Chief Investigator. At the baseline appointment, the Chief Investigator will randomise participants to either the intervention or control group after obtaining informed consent to participate in the trial.

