**Fig. 1 Fig1:**
[figure not shown]
Diagram of participant flow

The total period of data collection for participants is 12 weeks. Participants who are enrolled in the trial will attend a baseline appointment at La Trobe University Health Sciences Clinic to complete outcome measures and commence podiatry treatment or receive the control intervention depending on their allocation. All outcomes will be completed on a computer and recorded in REDCap except for goals developed for Goal Attainment Scaling, which will be recorded on hard copy sheets for each individual participant. The change in Goal Attainment Scaling (rather than the goal itself) will be recorded by the Chief investigator in REDCap at the week 12 follow-up assessment. At week 6, the research assistant will send outcome measures to participants by email with a link to the REDCap survey. Follow-up assessment at week 12 will be in-person at the La Trobe University Health Sciences Clinic. Participants who are randomised to the intervention group will also attend treatment visits at the La Trobe University Health Sciences Clinic, which will occur depending on the treatment required.

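### Randomisation is tied only to consent, so the arm may be known when Goal Attainment Scaling goals are set and baseline questionnaires answered

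*Protocol article*

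**What the plan says.** **Trigger for randomisation.** Methods: "Participants will be randomised to their intervention after completing consent at the baseline assessment". Procedures, on the baseline appointment: "the Chief Investigator will randomise participants to either the intervention or control group after obtaining informed consent to participate in the trial". These are the two places that give an order, and both name consent as the step that must come first.

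**Concealment.** Methods: "Allocation will be concealed from all researchers until after eligibility screening". Procedures describes that screening as a telephone interview by a research assistant, held before the baseline appointment.

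**The baseline visit.** After Fig. 1, Procedures says that participants attend "to complete outcome measures and commence podiatry treatment or receive the control intervention depending on their allocation". Study groups places triage of participant needs at the same assessment. Table 2 lists "Goal Attainment Scaling Baseline and week 12", so goals are also set at this visit.

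**Blinding.** Methods: "only participants will be blind to their allocation". Participants are blinded by limited disclosure, but the intervention group is told about its extra access to podiatry.

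**Goal records.** Every other outcome is completed on a computer. Goals are the exception, "which will be recorded on hard copy sheets for each individual participant". The change in goal attainment "will be recorded by the Chief investigator in REDCap at the week 12 follow-up assessment".

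**The concern.** A Goal Attainment Scaling score depends on how demanding the goals and their levels are made, and on who judges attainment. If the arm is known when goals are written, goals in the podiatry arm may be set with the coming treatment in mind while those in the control arm are not. Different goal difficulty would then appear as a between-group difference. Baseline questionnaires answered after allocation have a similar weakness, because they are no longer certain to be unaffected by the arm.

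The consequence falls on the goal-attainment effect size. The Discussion makes it an objective to learn whether this scale can serve as a primary outcome, and says the trial will supply data for the later sample size. Statistical analysis treats d of at least 0.20 as a signal of efficacy, so a small distortion is enough to matter. The Discussion itself names the subjectivity of goal assessment as a challenge, but the article ties no safeguard to it.

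**Working it through.** **1. The order of steps, from the text**

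| Step | Where stated | Must it precede allocation? |
|---|---|---|
| Telephone eligibility screening | Methods; Procedures | Yes |
| Consent at the baseline visit | Methods; Procedures | Yes |
| Baseline questionnaires | Procedures, after Fig. 1 | Not stated |
| Triage | Study groups | Not stated |
| Goals and attainment levels | Table 2; Procedures | Not stated |
| Start of allocated treatment | Procedures, after Fig. 1 | Follows allocation |

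The three middle steps have no fixed position relative to allocation. A team that randomised directly after consent and then set goals would be following the protocol. With goals on paper, the described records also give no electronic time stamp to show which came first.

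**2. The plan's sample size**

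Inputs: 12 per group and 20% drop-out (section on patient and public involvement). 12 / (1 − 0.20) = 15 per group, 30 in total. This matches the plan and is not in dispute.

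**3. How much a shift in goal difficulty could matter (illustration)**

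Assumed, not from the documents: standard T-score, k equally weighted goals, inter-goal correlation 0.3, SD 10.

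T = 50 + 10 × Σx / √(0.7k + 0.3k²), so a one-level shift in one goal adds 10 / √(0.7k + 0.3k²):

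| Goals k | 0.7k + 0.3k² | Points added | As d (SD 10) |
|---|---|---|---|
| 1 | 1.0 | 10.0 | 1.00 |
| 2 | 2.6 | 6.2 | 0.62 |
| 3 | 4.8 | 4.56 | 0.46 |
| 4 | 7.6 | 3.63 | 0.36 |

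The d column applies if everyone in one arm and no one in the other is shifted. The plan's threshold, d = 0.20, is 2.0 points. With three goals, 2.0 / 4.56 = 0.44, and 0.44 × 15 = 6.6, so about 7 of 15 participants in one arm.

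**4. Chance of seeing the efficacy signal with no true effect**

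Observed d ≥ 0.20 is equivalent to t ≥ 0.20 × √(n/2). With an arm-dependent shift of b SD, t is noncentral with 2n − 2 degrees of freedom and noncentrality b × √(n/2). The values of b are assumptions.

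| b (SD) | 12 per group | 15 per group |
|---|---|---|
| 0 | 0.315 | 0.294 |
| 0.1 | 0.406 | 0.394 |
| 0.2 | 0.502 | 0.502 |
| 0.3 | 0.599 | 0.609 |
| 0.5 | 0.770 | 0.795 |

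The b = 0 row is what remains when the score does not depend on arm. The signal still appears about 3 times in 10, so the fragility of the threshold is a separate matter. The concern here is the rise from that row.

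**The case against.** The protocol does not state a wrong order. Randomising after consent sets an earliest point and does not prevent measures and goals from coming first. The sentence on the baseline visit names outcome measures before treatment. Fig. 1 and Online Resource 2 were not available and may settle the order and the rating procedure. The concealment wording may simply be loose, since allocation comes from the REDCap module operated at the visit. Unblinded assessment is a declared choice for a feasibility trial.

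Much of this stands, and it rules out several stronger readings that a reader might draw:

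- *Goals are set after allocation.* The text permits this but does not say it.
- *The Chief Investigator rates attainment.* The text says only that this person records the change. That could be data entry of a rating made by, or agreed with, the participant.
- *Scores per goal are not kept.* The text says that the change, not the goal itself, is entered in REDCap. That does not show that levels per goal are discarded.
- *The feasibility conclusion is biased.* None of the ten Table 1 criteria uses a goal score or Cohen's d, and domain 10 rests on consumer interviews.

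The objection does not remove the gap. The article states the randomisation trigger twice and concealment once, and none of these statements covers baseline measurement. Participant blinding does not close the gap either, because intervention participants are told of the podiatry access and the article does not place that disclosure after goal setting.

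**Conclusion.** The concern holds as a gap in the randomisation rule. Followed as written, the rule allows goals to be set and baseline questionnaires answered with the arm known to the Chief Investigator, and possibly to intervention participants. The exploratory goal-attainment effect size and the data for the next trial are exposed; the feasibility criteria are not.

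The possible size is illustrative only. It rests on the assumed number of goals, weights, correlation, SD and share of participants shifted. Under those assumptions, a shift in under half of one arm equals the whole d = 0.20 threshold, and a 0.2 SD shift raises the chance of seeing the signal from 0.29 to 0.50 at 15 per group. The documents do not show that any such shift will occur.

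This should be fixed, but it is not a must-fix. If the figure or supplement already puts goals before allocation, stating that in the text and time-stamping the goals settles the baseline part.

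**What to change.** - **Randomisation rule (Methods and Procedures).** State that allocation stays concealed until, and randomisation occurs only after, consent, all baseline questionnaires, triage, and goals with all attainment levels are completed and saved with a time stamp in REDCap.
- **Week 12.** Store the attained level for each goal, and state who rates it. Having the participant mark the level before discussion with the Chief Investigator would limit investigator influence.
- **Reporting.** If assessment stays unblinded, report the goal-attainment effect size with that limitation.

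The cost is a reordering of steps within one visit and one added REDCap form, with no extra staff and no change to the 15 per group. Participant marking makes the outcome self-rated and still not fully blind, because intervention participants know of the podiatry access. The change has to be made before enrolment: the order in which goals and allocation occurred cannot be reconstructed afterwards from undated paper sheets.

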Treatment will be provided by a podiatrist with over 10 years of experience in clinical practice, who is endorsed to prescribe scheduled medicines, has undertaken further training in rheumatological conditions, and plays an active role in the Australian Rheumatology Association. For participants who require foot orthoses, Formthotics™ (Foot Science International, Christchurch, New Zealand) full length prefabricated foot orthoses will be provided. These are manufactured from a dual-density polyethylene closed cell foam that has a firm-density bottom layer (Shore-A durometer 50), and a soft-density top layer (Shore-A durometer 25). Participants will be provided the foot orthoses in accordance with the manufacturer’s instructions by selecting an appropriate size, heating the foot orthoses using a specifically designed machine from Foot Science International, placing them within the participants footwear, and asking participants to stand to allow the foot orthoses to mould to the contour of the foot. Adjustments to the foot orthoses will be made to ensure the participants agree they are comfortable. Participants who require footwear will be provided with a $250 discount from the cost of new footwear. The footwear will be agreed with the podiatrist and participants will be required to attend pre-arranged footwear suppliers to receive the discount. Advice provided to participants about footwear is included in Online Resource 1. All other treatment, such as skin or nail care, exercises, or other aids, will be provided in line with standard podiatry practice in Australia.

The control group will receive usual care plus a self-management package based on advice from Creaky Joints Australia (29 Tips from Podiatrists for Managing Arthritis Pain in Your Feet), which provides a range of education including regular self-inspection of feet, advice about exercising to reduce foot/ankle discomfort, selecting appropriate footwear, and the use of supportive aids such as foot orthoses, ice packs, salt baths etc. For usual care, participants will be advised they can seek any treatment they prefer over the 12-week duration of the trial and their progress will be monitored. At the conclusion of the trial, participants randomised to the control group will be invited to attend a debriefing session and will be offered the same treatment as the intervention group if the intervention is found to be effective.

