One UK-based randomised trial has evaluated podiatry care for people with rheumatoid arthritis [24]. This exploratory trial randomised participants to receive podiatry-led foot care for 12 months or a no treatment control group. The authors reported several considerations for the design of future fully powered randomised trials that we have considered during the design of this trial. First, the findings suggest that podiatry-led foot care maintains but does not improve foot-related impairment or disability in patients with stable, controlled rheumatoid arthritis. These findings suggest that podiatry-led care is important for maintaining foot health. A consideration for these findings was the use of a standardised outcome measure (the Leeds Foot Impact Scale) that may not be responsive to change [25]. Therefore, selecting an outcome measure that is both meaningful for patients and sensitive and responsive is important. Our feasibility trial includes multiple patient-centred outcome measures to allow evaluation of their performance for a larger randomised trial. Second, the trial faced difficulties recruiting participants due to stringent criteria for stable drug management and co-morbid diseases such as diabetes and peripheral vascular disease. The authors reported the criteria were too strict and therefore excluded many potential participants. For our feasibility trial, the inclusion criteria are broader and include any rheumatological condition without excluding participants with comorbidities. Third, more than one-third of patients refused to participate in the trial, mainly due to additional clinic visits, lack of understanding of podiatry care, and concerns about the non-intervention arm. Clear communication about the benefits and risks of podiatry care is therefore essential.

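### The trial is called participant-blind, but intervention participants are told of their podiatry access and so know their own treatment

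*Protocol article*

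**What the plan says.** The Abstract, the opening of Methods and the last paragraph of the Discussion all describe the trial as blinded for participants. In Methods: "This will be a pragmatic, participant-blind, parallel-group, randomised feasibility trial comparing access to a podiatry service with usual care". No other party is blinded: "Given this is a feasibility trial, only participants will be blind to their allocation".

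The mechanism follows: "Both groups will be blind to group allocation through limited disclosure". The next sentence says what is disclosed. "All participants will be informed that two different types of treatment are being compared", but "only the intervention group will be informed about the additional access to podiatry treatment".

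Under Study groups, the intervention arm receives podiatry care chosen by individual triage, with moulded orthoses or a footwear discount where required. Procedures adds treatment visits for that arm as needed. For the other arm, "The control group will receive usual care plus a self-management package based on advice from Creaky Joints Australia". Under usual care, "participants will be advised they can seek any treatment they prefer over the 12-week duration of the trial", and a debriefing for controls is placed at the end of the trial.

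Procedures has the Chief Investigator randomise participants and also enter the Goal Attainment Scaling change at week 12. Statistical analysis treats d ≥ 0.20 as a signal of efficacy.

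**The concern.** Blinding to allocation means that a participant cannot tell which of the compared treatments they have. A person who knows that two treatments are being compared, and is told that theirs includes extra podiatry access, can tell. What is withheld from that person is the content of the other arm, which is a different and weaker property.

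The distinction matters here for three reasons. Participant blinding is the only blinding the protocol claims. The Table 2 measures are self-reported, or in the case of Goal Attainment Scaling built on patient-set goals, and Goal Attainment Scaling is the candidate primary outcome for the larger trial. The results are also meant to signal efficacy and to supply data for the next sample size. A planner who takes the label at face value would discount expectation bias that the design does not remove.

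**Working it through.** **Step 1. Who knows what, by arm.**

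| Question | Intervention arm | Control arm |
|---|---|---|
| Told that two treatments are compared (Methods) | Yes | Yes |
| Told of the extra podiatry access (Methods) | Yes | No |
| Care received (Study groups) | Individual podiatry care, possibly orthoses or a footwear discount | Usual care plus self-management package |
| Extra treatment visits (Procedures) | Yes, as needed | None described |
| Can know own treatment | Yes | Knows it has a package and usual care |
| Can be unaware of the other arm's content | Possibly | Possibly |

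The statement that both groups are blind to allocation fails for the intervention arm on the text alone. Nothing in the text shows that it fails for controls: the package and the clinic assessments can pass as one of the two treatments.

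**Step 2. Who records the outcomes.** Table 2 lists 11 measures. Ten are questionnaires or rating scales answered by the participant. The eleventh, Goal Attainment Scaling, is recorded by the Chief Investigator, who also carries out the randomisation and so knows the allocation. For the intervention arm, neither the respondent nor the recorder is blind.

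**Step 3. The plan's own figure.** The sample size section starts from 12 per group and allows for 20% drop-out: 12 / (1 − 0.20) = 15 per group, 30 in total. This reproduces exactly and is unaffected by the blinding point. No alpha, power, SD or target difference is stated, so there is no power figure to check.

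**Step 4. What an expectation bias could do to the efficacy signal (illustration).** Inputs from the plan: the threshold d ≥ 0.20, 1:1 allocation, and n = 12 (after drop-out) or 15 (as recruited) per group. Assumed: normally distributed outcomes with a common SD, a true treatment effect of zero, and a reporting bias of b SD in favour of the intervention. The document gives no value for b, so a range is shown.

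With s = √(2/n), the observed d equals t × s. Hence P(observed d ≥ 0.20) = P(T ≥ 0.20/s), where T is non-central t with 2n − 2 degrees of freedom and non-centrality b/s.

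- n = 12: s = √(2/12) = 0.408, cut-off 0.20/0.408 = 0.490, 22 df.
- n = 15: s = √(2/15) = 0.365, cut-off 0.20/0.365 = 0.548, 28 df.

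| Assumed bias b (SD) | n = 12 per group | n = 15 per group |
|---|---|---|
| 0 | 0.315 | 0.294 |
| 0.1 | 0.406 | 0.394 |
| 0.2 | 0.502 | 0.502 |
| 0.3 | 0.599 | 0.609 |
| 0.5 | 0.770 | 0.795 |

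These are probabilities for a single outcome. The first row comes from the low threshold and the small groups, not from blinding. The part due to bias is the rise above that row: at b = 0.2, 0.502 − 0.315 = 0.187 (n = 12) and 0.502 − 0.294 = 0.208 (n = 15).

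**Step 5. Whether Table 1 covers it.** None of the ten feasibility criteria asks whether limited disclosure held.

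**The case against.** The best reply is that the mechanism is printed directly after the label, so anyone who reads Methods sees who is told what. No sentence claims that blinding protects the self-reported outcomes; that protection is only implied by the label. Feasibility is the main outcome, no Table 1 criterion turns on blinding, and the size of the bias is assumed. All of this is true, and it limits the consequence. It does not remove the contradiction, because the claim and the disclosure that defeats it stand side by side. The label also appears alone in the Abstract, where the disclosure is not given.

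Four stronger readings are tempting, and the document does not support them.

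- A reader might infer that blinding is not checked anywhere. That cannot be shown: the article says that acceptability and credibility of the interventions are collected and refers to Online Resource 2, which is not available here. Only the absence from Table 1 can be verified.
- A reader might infer that the whole trial is unblinded, or that the self-management package reveals the allocation to controls. The package may do the opposite, by giving controls a plausible treatment, and controls are not told of the podiatry service.
- A reader might see a contradiction with the Discussion, which says of recruitment: "Clear communication about the benefits and risks of podiatry care is therefore essential". That sentence responds to refusals in an earlier trial and does not require that each participant learn the other arm's content. It is a tension with limited disclosure, no more.
- A reader might infer that the definitive trial depends on limited disclosure. The protocol does not say so.

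**Conclusion.** The point holds for the intervention arm. Participants in that arm know their own treatment, so participant-blind is wrong as written for them, and no supplementary document could cure this. Limited disclosure may still work for controls.

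The consequence is that differences on all 11 Table 2 measures are open to expectation bias, with Goal Attainment Scaling further exposed through a recorder who knows the allocation. The size of the bias cannot be taken from the document. Under the stated assumptions, a bias of 0.2 to 0.3 SD with no treatment effect would move the chance of meeting the d ≥ 0.20 signal on one outcome from about 0.29–0.32 to about 0.50–0.61. Relabelling changes none of these probabilities; it changes how far the signal is trusted.

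The matter is moderate. It does not threaten the feasibility objective, but a prominent design claim is incorrect, it bears on how the efficacy data are used, and it is easy to correct.

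**What to change.** 1. In the Abstract, Methods and Discussion, replace participant-blind with a description such as: limited disclosure; controls are not told of the podiatry service; intervention participants and the recorder of Goal Attainment Scaling know the allocation.
2. In Statistical analysis, state that the d ≥ 0.20 signal, and any effect size used to plan the definitive trial, are not protected by blinding.
3. Add one REDCap item at week 12, before the control-group debriefing, that asks which treatment the participant believes was being tested and whether they received it. Report it by group as a feasibility result. It will inform mainly on controls, since intervention participants know their treatment. If Online Resource 2 already contains such an item, say so instead.
4. Add a sentence that reconciles limited disclosure with the Discussion's call for clear communication about podiatry care.

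The cost is a few changes of wording and one extra question. The design description becomes less favourable. The sample size, schedule and analysis of the other outcomes are unchanged.
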